## Abstract

**Purpose:**

(1) Exploring the evaluation and correlation of peripheral central auditory function in patients with chronic tinnitus. (2) Evaluation of the cumulative effect of acupuncture on peripheral central auditory function in patients with chronic tinnitus.

**Method:**

Our research is structured as a regulated and randomized trial with assessor blinding. Seventy-two participants who qualify with chronic tinnitus will be allocated in a 1:1 ratio to either the acupuncture group or the sham acupuncture group. Additionally, we will recruit 15 healthy individuals as subjects for data collection to observe the correlation of peripheral-central auditory function under different physiological states.

**Result:**

Clinical result metrics encompass the Tinnitus Handicap Inventory (THI), ABR testing, and fNIRS data collection. Evaluations will be carried out at baseline, after 10 treatment sessions.

**Conclusion:**

This research are anticipated to improve our comprehension of the effectiveness and fundamental processes of acupuncture in addressing persistent tinnitus and deeply explain the mechanism of action of the acupuncture method on chronic tinnitus.

**Clinical trial registration:**

ClinicalTrials.gov, identifier NCT06401993.

## Introduction

Tinnitus is the perception of one or more sounds without the presence of an outside sound source (1). The latest European tinnitus guidelines consider a duration of up to 3 months as the acute phase, 3–6 months as the subacute phase, and over 6 months as the chronic phase (2). The global prevalence of tinnitus ranges from 5.1 to 42.7%, and the incidence rate in mainland China is consistent with the global data, at 4.3–51.33% (3). Chronic tinnitus can impact individuals’ employment, auditory perception, emotional state, and sleep patterns, while severe cases may result in psychiatric disorders and even suicidal tendencies (4). Due to the unclear pathogenesis of tinnitus, current clinical treatments mainly include pharmacotherapy, sound therapy, and habituation therapy, however, there is no conclusive evidence to support the efficacy of these treatment options (2, 5), hence most patients with tinnitus progress to the chronic phase. Therefore, delving into the key mechanisms underlying chronic tinnitus and seeking effective treatment methods has always been a hot topic in auditory neuroscience research.

The occurrence of tinnitus is related to abnormal auditory nerve function. Some studies have reported that changes in the excitation threshold of cochlear hair cells may lead to tinnitus (6), especially when there is a decrease in the number of ribbon synapses on cochlear hair cells. This results in a reduction in the level of neurotransmitter release in the synaptic cleft, a decrease in signals transmitted to the auditory central system, and an abnormal increase in central excitability, leading to tinnitus (7). It is important to note that tinnitus is not solely caused by changes in cochlear activity but also originates from higher-level structures within the auditory nerve pathway. The removal of the cochlea or dorsal cochlear nucleus in guinea pigs after long-term exposure to noise does not alter the hyperpolarized electrical activity of the auditory center, indicating that tinnitus can exist independently without the influence of the periphery (8). Clinically, it has also been reported that long-term tinnitus patients do not experience a disappearance of tinnitus symptoms after surgical transection of the cochlear nerve (9). In addition, recent studies have shown that brain structures outside the auditory nervous system, including the limbic system, parietal lobe, and frontal lobe, are also involved in the maintenance process of tinnitus (10, 11). These areas may mediate the perception of tinnitus through their influence on cognition, emotion, and behavior (12). Therefore, it is currently believed that the periphery (cochlea) is the initial site of tinnitus generation, and the central plasticity changes it triggers are key factors in the occurrence of tinnitus. Hence, tinnitus is also considered a “central reorganization disease” (13).

Auditory brainstem response (ABR) is a bioelectric response of the brainstem evoked by sound stimulation, reflecting the highly synchronized activity of the auditory center from the cochlea to the brainstem. It can sensitively locate damage to the auditory nerve and brainstem conduction pathways (14). ABR consists of seven waveforms, among which waves I, III, and V are the most stable and prominent in the ABR waveforms. In animal models, it has been confirmed that the amplitude of wave I of ABR is related to the number of ribbon synapses in the cochlear hair cells and nerve fibers (15). In clinical trials, it has also been confirmed that the amplitude of wave I of ABR is related to tinnitus symptoms (16). Therefore, ABR can objectively reflect the patency of the peripheral auditory conduction pathway and the normality of brainstem function, and can be used as an objective evaluation index for tinnitus. However, the relationship between ABR and tinnitus still needs further clarification.

Functional Near-Infrared Spectroscopy (fNIRS) is a new non-invasive technique for brain functioning imaging that has emerged in recently. fNIRS can immediately and in real-time ascertain the cognitive cortex’s hemodynamic activity, and infer the neural activity of the brain based on this. In recent years, researchers have begun to use fNIRS to explore the mechanisms related to tinnitus, and preliminary findings have shown that patients with tinnitus have abnormal neural functional connectivity strength between the auditory center and various cerebral areas such as the temporal–parietal and parietal lobes (17). Numerous studies have confirmed that the brain activity obtained using fMRI is highly correlated with the fNIRS signals in the same region, indicating the authenticity and accuracy of the detection results of fNIRS (18, 19). Moreover, compared with fMRI, fNIRS is more sensitive to changes in functional activity of the cerebral cortex, has a higher temporal resolution, and can track changes in brain functional activity at all times and throughout the process. Most importantly, its silent examination characteristic makes it more suitable as an examination method related to hearing.

Acupuncture is a convenient and low-side-effect complementary therapy that has long been used to treat tinnitus, especially in China. Some systematic reviews and meta-analyses generally support the effectiveness and safety of acupuncture in treating tinnitus (20–23). With in-depth research, more and more evidence suggests that acupuncture can significantly improve tinnitus symptoms (24, 25). Studies have also found that acupuncture can improve tinnitus by regulating central neurotransmitters, such as gamma-aminobutyric acid and serotonin and their receptors, thereby inhibiting or activating specific components of the auditory system (26). Recently, literature has reported that acupuncture at corresponding acupoints can enhance the blood oxygen content in the auditory cortex and activate the auditory cortex of tinnitus patients, as observed by fNIRS, preliminarily elucidating its mechanism of action in treating tinnitus (27). However, there is currently a lack of sufficient evidence to support the exact mechanism of acupuncture in treating tinnitus, especially the relationship between the therapeutic effects of acupuncture and the auditory conduction pathway and brain functional activity in tinnitus is still unclear and requires further in-depth research. Moreover, due to tinnitus being a patient-reported subjective symptom, there are no objective evaluation techniques available to objectively analyze the healing benefits of individual remedies for improving tinnitus. In light of these study deficiencies, functional near-infrared spectroscopy (fNIRS) and auditory brainstem response (ABR) may yield significant insights.

Given the significant potential of fNIRS and ABR in tinnitus research, and the constraints of prior studies, we have developed this randomized controlled experiment (RCT) to investigate the pathological mechanisms of chronic tinnitus using fNIRS and ABR. The objectives of this trial are: (1) To compare the auditory brainstem response parameters and extracerebral oxygen levels of the cerebral cortex between chronic tinnitus patients and healthy subjects, and to compare the correlation of peripheral-central auditory function under different physiological states. (2) To compare the intervention effects of acupuncture versus sham acupuncture on chronic tinnitus patients from clinical manifestations, ABR parameters, and extracerebral oxygen levels of the cerebral cortex, exploring the correlation of acupuncture intervention on chronic tinnitus from the peripheral-central auditory function at three levels: clinical, target organ, and central.

## Materials and methods

### Study design

Our research is structured as a regulated and randomized trial with assessor blinding. Seventy-two participants who qualify with chronic tinnitus will be allocated in a 1:1 ratio to either the acupuncture group or the sham acupuncture group. Additionally, we will recruit 15 healthy individuals as subjects for data collection to compare the auditory brainstem response parameters and extracerebral oxygen levels of the cerebral cortex between chronic tinnitus patients and healthy subjects, and to observe the correlation of peripheral-central auditory function under different physiological states. Our protocol’s reporting complies with the Standard Protocol Items: Recommendations for Interventional Trials (SPIRIT) criteria. The SPIRIT for the study is shown in Figure 1, and the flowchart is shown in Figures 2, 3.

**Figure 1 fig1:**
[figure not shown]
The SPIRIT schedule of enrollment, interventions, and assessment.

**Figure 2 fig2:**
[figure not shown]
Part one flow chart of the study process.

**Figure 3 fig3:**
[figure not shown]
Part two flow chart of the study process.

### Participant recruitment

Individuals who satisfy the eligibility requirements for chronic tinnitus will be recruited from the outpatient departments of Otorhinolaryngology and Acupuncture at the Zhejiang Chinese Medical University’s third affiliated hospital. Before signing the informed consent form, each participant will receive a comprehensive explanation of the protocol.

#### Diagnostic criteria

Diagnosing tinnitus follows international criteria, which characterize it as the perception of sound without an external auditory stimulus. Additionally, according to the multidisciplinary European guidelines on tinnitus, tinnitus is referred to as “chronic” when its duration is 6 months or longer (2).

Unlike objective tinnitus, subjective tinnitus can only be perceived by the patient and cannot be assessed via auscultation by a physician.Patients perceive ear noises without the assistance of an outside source; these noises may be continuous or sporadic and can exhibit diverse auditory characteristics, including ringing, buzzing, clicking, or roaring.Otoscopic examination reveals no abnormalities in the ears, encompassing the eardrum and canal.Tinnitus affects the patient’s the norm of living to some extent, and the degree of annoyance varies from person to person.

#### Inclusion criteria

Patients with chronic tinnitus, defined as a duration of the tinnitus of 6 months or longer (2).No contraindications for fNIRS scanning.Individuals aged between 20 and 55 years, who are right-handed.Patent external auditory canal and intact eardrum.The average hearing threshold in both ears is less than 35 dB.Normal expressive and comprehension abilities.

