#### Exclusion criteria

History of drug dependence or alcohol addiction.Severe central nervous system diseases or other systemic diseases such as cardiovascular and cerebrovascular conditions.Organic lesions such as craniocerebral trauma.Inner ear or auditory nerve diseases such as sudden deafness, Meniere’s disease, otosclerosis, or auditory neurinomas.External ear or middle ear related diseases such as otitis externa, acute/chronic otitis media.Patients with auditory hyperacusis.

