#### Exclusion criteria for healthy subjects

Pregnant or breastfeeding women, or those who plan to conceive within the next 6 months.Individuals with a history of head trauma.No metallic implants in the body and no contraindications for fNIRS testing.Those who are taking part in more clinical studies at the moment.

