#### Allocation concealment and randomization

Suitable participants will be assigned at random to the acupuncture group or the sham acupuncture group in a proportion of 1:1 using a random stratification block design by gender and lifetime, with the Statistical Product and Service Solutions Version 25.0 (SPSS Inc., Chicago, IL, USA). An impartial administrator, uninvolved in other study protocols, will conduct this process, and the details of the list of random allocations will remain completely confidential. This randomization results will be preserved in opaque, sealed, envelopes with sequential numbers to guarantee allocation concealment.

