### Intervention procedures

All participants with chronic tinnitus will receive acupuncture treatment for a total of 10 times (Acupuncture treatment is given once every 2–3 days, and it takes about 28 days for 10 treatments). We chose 10 acupuncture times based on our previous research and clinical experience of acupuncture in the treatment of tinnitus (28, 29). We believe that the methods are representative and can effectively evaluate the efficacy of acupuncture in the treatment of tinnitus. After the completion of 10 acupuncture times, we will follow up the patients within 3 months in order to more comprehensively evaluate the efficacy of acupuncture. In this context, patients in the acupuncture group should ensure the occurrence of “de qi” (a sensation of numbness, tingling, and heaviness that arises after the acupuncture needle is inserted into the body (30)) after needling the acupoints. We use CT positioning. The therapeutic group has a puncture depth of about 20–25 mm, with the needle tip reaching the temporomandibular joint (see Figure 4). Needling techniques are applied to generate “de qi” and produce a therapeutic effect. While patients in the sham acupuncture group are not required to achieve “de qi.” The acupuncture depth of the placebo group is about 5-8 mm, and the needle will not reach the treatment depth. Acupuncture techniques will not be used, and “de qi” will be not produced. What is more, in sham acupuncture, we use precise needle insertion positions and applied force to avoid interference with the actual therapeutic effect on patients. Acupuncture depth only produces therapeutic effects when it reaches a certain depth, as shown in Figure 4 (31).

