### Acupuncture group

Acupuncture points prescription: The points to be used include Yifeng (affected side), Tinggong (affected side), Tinghui (affected side), Wai Guan (both sides), Zhongzhu (both sides), and Hegu (both sides) and so on. The participants in this study are licensed acupuncturists possessing more than 10 years of medical expertise of acupuncture. To guarantee strict compliance with the usual procedure for acupuncture, all professionals will undergo specific instruction on the acupuncture practices prior to the study. They will receive a booklet detailing the standardized procedures. Each acupoint will be located according to the WHO standards (32). For specific location, see Table 1.

**Table 1 tab1:** Locations of the selected acupoints.

Acupoints	Location
Yifeng (TE17)	Behind the earlobe, between the mastoid process and the mandible.
Tinggong (SI19)	In front of the tragus, when the mouth is open, at the depression.
Tinghui (GB2)	In front of the intertragic notch, at the posterior border of the condyloid process of the mandible.
Zhongzhu (TE3)	On the dorsum of the hand, between the 4th and 5th metacarpal bones, in the depression proximal to the MCP joint of the 5th digit.
Waiguan (TE5)	2 cun above the transverse crease of the wrist, between the ulna and radius bones.
Taixi (KI3)	In the depression between the medial malleolus and the Achilles tendon.
Xiawan (CV10)	2 inches above the navel, on the anterior midline.
Zhongwan (CV12)	4 inches above the navel, on the anterior midline.
Guanyuan (CV4)	3 inches below the navel, above the anterior midline.
Qihai (CV6)	1.5 inches below the navel, above the anterior midline.
Shangqu (KI17)	2 inches above the navel, with a 0.5 inch opening next to the midline.
Yindu (KI19)	4 inches above the navel, with a 0.5 inch opening next to the midline.
Hegu (LI4)	At the midpoint of the radial side of the second metacarpal bone.

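### Pregnancy is excluded for the healthy comparison group but not for the 72 needled patients, whose only printed contraindication item concerns the fNIRS scan

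*Protocol article*

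**What the plan says.** The protocol article prints separate eligibility lists for patients and for healthy subjects.

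- **Patients, Inclusion criteria.** Six items. One is a contraindication item: "No contraindications for fNIRS scanning". Another sets age and handedness: "Individuals aged between 20 and 55 years, who are right-handed".
- **Patients, Exclusion criteria.** Six items. The nearest to a general safety exclusion is "Severe central nervous system diseases or other systemic diseases such as cardiovascular and cerebrovascular conditions". Two others cover ear and auditory-nerve disease.
- **Healthy subjects, Exclusion criteria.** One item reads "Pregnant or breastfeeding women, or those who plan to conceive within the next 6 months". The list also mentions fNIRS contraindications.
- **Who is needled.** Under Intervention procedures, "All participants with chronic tinnitus will receive acupuncture treatment for a total of 10 times". Depth is about 20–25 mm at the ear points in the acupuncture group and 5–8 mm in the sham group. The Sham acupuncture group section keeps the same points and still penetrates the skin.
- **Where.** The Acupuncture group section names three ear points and three limb points, then leaves the list open. Table 1 gives 13 selected points, including Guanyuan and Qihai, both located below the navel.
- **Risk and medication.** Evaluation of safety names hemorrhage, bruising and infection among the harms of acupuncture. Concurrent intervention and care lets patients with chronic conditions stay on their usual drugs.

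**The concern.** The protection is placed where the exposure is lowest. The article screens patients for contraindications to a scan that its Introduction describes as non-invasive, but prints no such screen for the invasive treatment. It excludes pregnancy in the group recruited only for data collection and not in the group that is needled.

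What is at stake is participant safety. If the criteria are followed as printed, nothing decides before randomisation who should not be needled. Adverse-event recording acts only after harm. A practitioner who declines to needle someone after allocation loses a patient who is already randomised.

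**Working it through.** No arithmetic beyond counting applies. The check is a reading of the printed lists, then of the rest of the article for any rule that fills the gap.

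**Step 1: count the items.** Patient criteria: 6 inclusion + 6 exclusion = 12.

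| Topic | Patient lists (12 items) | Healthy-subject exclusion list |
|---|---|---|
| fNIRS contraindication | 1 | 1 |
| Needling contraindication | 0 | 0 |
| Pregnancy, breastfeeding, planned conception | 0 | 1 |

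**Step 2: set exposure beside protection.**

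| Group | Number | Needled? | Pregnancy excluded? |
|---|---|---|---|
| Acupuncture | 36 | yes, 10 sessions | no |
| Sham | 36 | yes, 10 sessions, 5–8 mm | no |
| Healthy | 15 | not described | yes |

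Needled patients without a printed pregnancy rule: 36 + 36 = 72.

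**Step 3: is pregnancy possible among patients?** Yes. The age range is 20 to 55, neither sex is excluded, and allocation is made "using a random stratification block design by gender and lifetime", so women are expected in the sample.

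**Step 4: does any likely purpose of the healthy-subject item justify the difference?** The article gives no purpose. If it is safety, the needled group has the stronger claim. If it is measurement quality or a clean physiological reference, patients undergo the same ABR and fNIRS tests and are compared with the healthy group on them. Either reason would carry the item over to patients.

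**Step 5: what do the existing exclusions cover?**
- Normal otoscopy (Diagnostic criteria) and the ear-disease exclusions deal with the ear itself. They do not reach the limb points or the abdominal points in Table 1.
- The systemic-disease exclusion plausibly removes bleeding disorders, and some patients anticoagulated for cardiovascular or cerebrovascular disease. It cannot be relied on at full breadth, because Concurrent intervention and care foresees enrolled patients with hypertension, diabetes and other chronic conditions on their standard drugs.
- Neither exclusion covers pregnancy.

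**Step 6: does another section supply the missing rule?** Contraindications appear twice in the article, both times for fNIRS: "No contraindications for fNIRS scanning" for patients and "no contraindications for fNIRS testing" for healthy subjects. Pregnancy appears once, for healthy subjects. The sections on randomisation, intervention, concurrent care, safety, ethics, data handling and monitoring add no rule on either.

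**The case against.** The strongest reply is that this is a condensed article and that the full protocol may hold the missing criterion. The printed patient list is visibly incomplete in one respect: signed consent is listed as a criterion only for healthy subjects, yet patients plainly must consent. On that view, an item found only in the healthy list does not show that it is absent for patients. The healthy exclusion list is also loosely drafted, since it lists the absence of fNIRS contraindications as a reason to exclude, so it is a weak guide to intent.

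Part of this stands. The full protocol is not shown, and the point can concern only the printed criteria. The consent example does not carry over, however. Patient consent is supplied elsewhere, under Participant recruitment and under Ethical approval and study registration. No section supplies a pregnancy or needling rule for patients. The lists are itemised by group, and pregnancy is addressed for one group and not for the other.

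A second reply is that licensed acupuncturists with more than 10 years' experience, trained for the study and given a procedures booklet, would use judgement. That is a real safeguard, but it is not an eligibility rule and need not act before randomisation.

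Several stronger readings are tempting, and the documents do not support them:
- *The pregnancy item is a needling safeguard attached to the wrong group.* Its purpose is not stated.
- *Needling in pregnancy is shown to be harmful, or the points below the navel are unsafe.* The article says neither. Because the prescription is open-ended, it is also unclear how often those points are used.
- *Every patient on any drug affecting bleeding should be excluded.* The text gives no basis for so broad a rule.
- *Temporomandibular joint disease must be excluded because the ear needles reach that joint.* This is a clinical inference that the article does not make.
- *Patients have no protection at all.* The ear-disease and systemic-disease exclusions cover part of the risk.

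**Conclusion.** The point holds for the criteria as printed. Pregnancy, breastfeeding and planned conception are excluded for 15 people who are not described as being needled, and not for the 72 who are needled in both arms. Of the 12 patient criteria, one is a contraindication item and it concerns fNIRS. The harms that make a needling check reasonable, hemorrhage and infection, are named by the article itself.

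The size is limited. The number of patients at risk cannot be derived and none is claimed. The gap is the same in both arms, and no estimate, power or error rate changes. The conclusion assumes that the lists are applied as printed. If the full protocol already has these criteria, the fault is only that the article's lists leave them out.

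**What to change.** Make two additions to the patient exclusion criteria:

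1. Extend the healthy-subject item on pregnancy, breastfeeding and planned conception to patients. Its 6-month horizon already exceeds the patient schedule of about 28 days of treatment plus follow-up within 3 months, roughly 4 months in all.
2. Add one exclusion for contraindications to needling: at least a bleeding disorder or anticoagulant treatment, and infected or broken skin at a needle site. Naming bleeding disorders removes any doubt about whether the systemic-disease item covers them. The clinical investigators decide on any further items.

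Check both before randomisation, identically for all patients, since the sham needle also penetrates the skin at the same points. If the full protocol already contains these rules, print them in the list.

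The cost is two lines of text, a short screening checklist and a few more screen failures. The sample size and the analysis stay as they are.
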